### Study locations

Most of the interventions will be carried out at three co-operating outpatient clinics and two inpatient wards, all places where traumatized children of immigrant background would in any case receive treatment. These clinics and wards are 1) the Family Counselling Centre of the City of Tampere, 2) the Psychiatric Clinic for Traumatized Children at Tampere University Hospital, 3) the Adolescent Psychiatry Clinic at Tampere University Hospital, 4) the Psychiatric Treatment and Research Unit for Adolescent Intensive Care (EVA) at Tampere University Hospital, and 5) the Centre for Torture Survivors (Helsinki Deaconess Institute). In addition, some participants may be recruited by and receive treatment from co-operating individual therapists operating privately.

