### Participants

The participants of the study are up to 80 children (between 9 and 17 years of age) living in Finland who will attend Narrative Exposure Therapy or treatment as usual for posttraumatic stress symptoms due to exposure to armed conflict. As no war or major organized violence has taken place in Finland for decades, these participants will be immigrants, refugees or asylum seekers. The sample will be collected among all eligible children who are clients of (a) The Family Counselling Center of the City of Tampere, (b) The Psychiatric Clinic for Traumatized Children at Tampere University Hospital, c) The Adolescent Psychiatry Clinic at Tampere University Hospital, d) the Psychiatric Treatment and Research Unit for Adolescent Intensive Care at Tampere University Hospital, e) The Centre for Torture Survivors of the Helsinki Deaconess Institute or f) co-operating individual private practitioners trained in NET.

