Due to restrictions on the use of the tests used for measurements of cognitive performance, these additional assessments will be carried out by a member of the research team (SK), a licensed clinical psychologist, and studied in a smaller subsample. For n = 20 participating children about to start treatment during 2015, willingness and informed consent to participate in these additional tests will be requested, and the measurements will then be carried out at T0 and T4 for this subsample.

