#### Effect evaluation

The main effect of NET as compared to TAU and the waiting list control condition on the primary outcomes of PTSD symptom severity, depressive symptoms, psychological distress, resilience and cognitive performance will be analysed employing analyses of covariance. Potential confounding factors (age, gender, treating unit) will be included as covariates. The main effects of NET as compared to TAU and the waiting list condition on the secondary outcomes of trauma memory quality and trauma-related cognitions will be similarly analysed employing analyses of covariance. For all analyses of covariance, effect sizes will be reported as partial η^2^, with 95 % confidence intervals included.

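### The covariate list set for all primary outcomes (age, gender, treating unit) also governs the 20-child cognitive tests, where the gender and unit terms are likely, but not certain, to cost precision

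*Protocol article*

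**What the plan says.** Effect evaluation lists the primary outcomes and their method together: "depressive symptoms, psychological distress, resilience and cognitive performance will be analysed employing analyses of covariance". The next sentence gives the adjustment set: "Potential confounding factors (age, gender, treating unit) will be included as covariates". It makes no exception for any outcome.

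The Procedure section restricts the cognitive tests to a subsample, described there as follows: "For n = 20 participating children about to start treatment during 2015". These children are asked for separate consent. On timing, the same section allows two test points only: "the measurements will then be carried out at T0 and T4 for this subsample".

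On the number of units, Study locations says "Most of the interventions will be carried out at three co-operating outpatient clinics and two inpatient wards" and then, after naming the five sites, adds a possible further source: "In addition, some participants may be recruited by and receive treatment from co-operating individual therapists operating privately". The Participants section likewise ends its list of sources with "f) co-operating individual private practitioners trained in NET".

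The article does not say how treating unit is coded, how many units supply the 20 tested children, or how strongly the three covariates predict the cognitive scores.

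**The concern.** An adjustment set that costs almost nothing with 80 children can be expensive with 20. Treating unit is the heavy item: entered as a factor, it takes four or five terms. With 20 children over five or six units there are three or four children per unit. In groups that small, arm and unit overlap by chance, and a unit whose tested children all fall in one arm contributes nothing to the arm comparison. Nothing in the Procedure section balances the 20 children by arm within unit.

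At stake is the width of the interval for one primary outcome. Randomisation already guards the comparison against systematic differences by gender and unit, so in this subsample those terms mainly have to justify themselves by reducing residual variance.

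**Working it through.** **The plan's own figure.** Sample size calculation gives 52 participants for alpha 0.05, f about 0.40 and power 0.80. The noncentral F calculation (numerator df 1, two groups, noncentrality f²N, denominator df N − 2 − covariates) returns N = 52 at f = 0.40 with 0, 1, 3, 6 or 7 covariates. The figure reproduces. It does not react to the number of covariates because the formula counts only lost degrees of freedom, not chance overlap between arm and covariates. At n = 20 and d = 0.85 (f = 0.425) it gives 0.44 with no covariates and 0.41-0.42 with 6-7. That calculation would therefore not have revealed the problem.

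**Parameter count.** Age 1, gender 1, unit 4 (five units) or 5 (six categories): 6 or 7 covariate terms. Adding intercept and arm gives 8 or 9 parameters, leaving 20 − 8 = 12 or 20 − 9 = 11 residual df.

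**Cost against age alone.** With q covariate terms explaining a share R² of the variance, the expected variance of the arm difference relative to no adjustment is (1 − R²)(n − 3)/(n − 3 − q). Age is kept in both models, so its contribution cancels. If gender and unit explain nothing further, the variance ratio of the full list to age alone is (n − 4)/(n − 3 − q):

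| Design | q | Variance ratio | SE ratio |
|---|---|---|---|
| n = 20, three units | 4 | 16/13 = 1.23 | 1.11 |
| n = 20, five units | 6 | 16/11 = 1.45 | 1.21 |
| n = 20, six categories | 7 | 16/10 = 1.60 | 1.26 |
| n = 80, five units | 6 | 76/71 = 1.07 | 1.03 |
| n = 80, six categories | 7 | 76/70 = 1.09 | 1.04 |

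These are averages over possible splits, pulled up by occasional bad ones, and they assume arm is drawn independently of unit. Simulation (ages uniform over 9-17, random gender and unit) gives a median SE increase of 8%, 16% and 21% for the three n = 20 rows. If arms are blocked within unit, the increase falls to about 4% with three units and about 8% with five or six. The working ranges are therefore 4-10% (three units), 8-22% (five or six) and 1-4% at n = 80. The interval widens slightly more than the SE because the t multiplier rises from 2.110 (17 df) to 2.179 (12 df) or 2.201 (11 df).

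**Break-even.** From the same formula, gender and unit together must explain 1 − 11/16 = 31% (five units) or 1 − 10/16 = 38% (six categories) of the variance left after age before they repay their cost in SE. With arms blocked within unit, simulation puts this at about 20%.

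**Illustrative power.** Take d = 0.85, five or six units, and gender and unit uninformative. Power is about 0.28-0.35 for the list as written and about 0.42 with age alone. With age and the T0 score it is about 0.50 if the T0-T4 correlation is 0.5, and 0.65 if it is 0.7. Both correlations are assumptions. Dropping gender and unit accounts for the step to 0.42; the T0 score accounts for the rest.

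**The case against.** A reader might infer that the listed covariates simply make the NET-TAU estimate less precise. The article does not support that. Against no adjustment at all, the full list breaks even when it explains 6/17 = 35% or 7/17 = 41% of the variance. At R² = 0.5 the SE ratio is √(0.5 × 17/11) = 0.88 or √(0.5 × 17/10) = 0.92, a gain. Over ages 9-17, age could plausibly explain much of a raw cognitive score. This stands, and it is why the comparison above keeps age in both models and charges only gender and unit.

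A reader might also count nine parameters as the covariates' own. Nine is the whole model with six unit categories; the covariates account for 6 or 7.

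Six categories is the top of the range. Private therapists are only a possibility, one research-team member does all the cognitive testing, and recruitment is mostly in the Tampere region. The 20 children may come from two or three units, where the cost is small. This stands.

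Nor should power at d = 0.85 be read as the plan's forecast for this outcome. Sample size calculation gives that value for PTSD severity, NET against waiting list, and says no effect estimate exists for TAU. It is borrowed here for scale only.

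Unit adjustment is also defensible in itself. The units range from a counselling centre to an intensive-care ward, usual care differs between them, and the allocation folders were held at the clinics. Its coding may be settled in a fuller plan. That makes simply dropping unit arguable, but the article still states one list for all primary outcomes with no exception for the one measured in 20 children.

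**Conclusion.** The point holds as a conditional, minor one. The rule as written covers the cognitive tests. At n = 20 its gender and unit terms are likely to cost precision compared with age alone: SE about 8-22% larger with five or six units, and 4-10% with three. This assumes that unit enters as a fixed factor and that gender and unit explain nothing beyond age. The cost shrinks or disappears if fewer units contribute, if arms are balanced within unit, or if gender and unit explain roughly 20-40% of the remaining variance. The article does not settle any of these. The list is close to harmless for outcomes measured in all 80 children. The main limit on the cognitive comparison remains the 20 children themselves, which no choice of covariates removes.

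**What to change.** In Effect evaluation, confine the age, gender and treating unit list to outcomes measured in all children. For WMTB-C, RPM and TMT, specify the primary model as the T4 score on arm, age and the T0 score of the same test, with treating unit omitted or collapsed to a single inpatient/outpatient term. Report the full age, gender and unit model as a sensitivity analysis. Fix this before outcome data are examined.

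The cost is one sentence and no new data, since the T0 tests are already scheduled. The downside is that, in this one subsample analysis, unit differences are covered by randomisation and the T0 score rather than by unit terms; the sensitivity analysis shows whether that matters.

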### Research questions and hypotheses

This study will address the effectiveness of NET in treating trauma-related symptoms and improving resilience and cognitive performance. The mediating roles of trauma-related cognitive appraisals and memory functions on this effectiveness will also be studied, as well as several moderators potentially affecting recovery. Accordingly, the research questions are as follows.Does NET reduce a) posttraumatic stress disorder symptoms, b) depressive symptoms and/or c) psychological distress symptoms in children traumatized by war more effectively than a waiting list condition or treatment as usual? Does NET increase resilience or improve cognitive performance?The hypothesis is that NET is more effective in reducing PTSD, depressive and psychological distress symptoms as well as in increasing resilience and improving cognitive performance than TAU or a waiting list condition, to a statistically and clinically significant degree.What changes in the participants’ trauma-related memory functions and cognitions can be observed as a result of NET treatment, as compared to a waiting list condition and treatment as usual?The hypotheses are that statistically significant differences between the NET group and the control groups will be found in the participants’ trauma-related memory functions and cognitions at the end of treatment. It is hypothesized that at the end of treatment, NET participants will show lower levels of overgeneralization and fragmentation in their autobiographical memories, as compared to baseline, as well as more spatial and temporal contextualization and coherence. The trauma memories of children after NET are expected to be less biased and intrusive as compared to controls, and include more verbal and fewer sensory elements. Finally, it is hypothesized that participants in the NET group exhibit greater reductions in dysfunctional trauma-related cognitive appraisals, as compared to the waiting list and TAU groups.To what extent do these changes in trauma-related memory functions and cognitions mediate the effectiveness of NET in reducing PTSD symptoms, depressive symptoms and psychological distress symptoms, increasing resilience and improving cognitive performance?The hypothesis is that beneficial changes in autobiographical memory, trauma-related memories and trauma-related cognitive appraisals partly explain the reduction in at least PTSD and depressive symptoms among children who participate in NET, and may contribute to increased resilience and improved cognitive performance.To what extent does level of peritraumatic dissociation, level of cognitive performance or gender moderate the effectiveness of NET in reducing trauma-related symptoms?The hypothesis is that participants with very high levels of peritraumatic dissociation benefit less from the intervention in terms of symptom reduction. Girls and children with higher levels of cognitive performance are hypothesized to benefit more from the intervention.

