### Statistical analyses

#### Basic analyses

The sample and its characteristics will be analysed employing descriptive statistical methods. Means, standard deviations and other basic statistics for all relevant variables will be calculated for descriptive purposes. Between-group comparisons at baseline will be performed to test randomization and assess differences between treatment and control groups, as well as between participants at different study locations. The internal reliabilities of the instruments used will be analysed employing Cronbach’s α. For all statistical tests, significance levels will be set at α = 0.05, with the Holm-Bonferroni method used to control family-wise error rates, where appropriate. Multiple imputation will be employed in the case of dropouts or other missing data. Intention-to-treat analyses will be carried out, so that all participants who are randomized into either group will be included in final analyses.

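### Partial η² is the only treatment-effect estimate given an interval, and it has neither sign nor scale units, so it cannot show the direction or clinical size of the NET effect

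*Protocol article*

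**What the plan says.** All references are to the protocol article.

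- **Effect evaluation.** Primary and secondary outcomes "will be analysed employing analyses of covariance". On covariates: "Potential confounding factors (age, gender, treating unit) will be included as covariates". For all of these models "effect sizes will be reported as partial η^2", with 95% "confidence intervals included". The method for constructing the interval is not named.
- **Basic analyses.** For all tests "significance levels will be set at α = 0.05", "with the Holm-Bonferroni method used to control family-wise error rates, where appropriate". The only other reporting named is: "Means, standard deviations and other basic statistics for all relevant variables will be calculated for descriptive purposes".
- **Research questions and hypotheses.** NET is expected to be better than TAU or the waiting list "to a statistically and clinically significant degree".
- **Ethical issues.** An interim look stops the trial if NET does worse than TAU by a clinically significant amount.

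No covariate-adjusted, signed estimate with an interval is named for any outcome.

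**The concern.** The main hypothesis makes two demands on the effect estimate. It must show which arm did better, and it must be readable against a clinical scale. Partial η² is a share of variance between 0 and 1. It takes the same value whichever arm is ahead, and it is not in CRIES, DSRS, SDQ or CYRM points. Its size also depends on how much residual variance the covariates leave. An interval around it therefore cannot show whether a benefit of a given number of points is supported or excluded.

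A smaller matter concerns agreement with the test. Partial η² is a function of F, and the F test rejects only in its upper tail. A two-sided 95% interval puts 2.5% in that tail, whereas the test uses 5%. A result can then be declared significant beside an interval that starts at zero.

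**Working it through.** **Inputs from the article.** α = 0.05; planned N = 80 with 1:1 allocation; covariates age, gender and treating unit; planning values d = 0.85, f ≈ 0.40, power 0.80 and required N = 52 (Sample size calculation).

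**Assumptions.** 40 children per arm, covariates balanced between arms, one numerator df. The residual df are not stated. With one df per covariate they are 80 − 1 − 1 − 3 = 75. With treating unit as a six-level factor (five named units plus private practitioners) they are 80 − 1 − 1 − 1 − 1 − 5 = 71. I use 70 and 75.

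**1. The article's own figure.** Power comes from the noncentral F with λ = f²N and numerator df 1. With f = 0.40, power is 0.7996 at N = 51 and 0.807 at N = 52. The stated 52 is reproduced, so a one-df F test fits the article's planning.

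**2. Sign.** With one numerator df, partial η² = t²/(t² + df). For t = +2.8 and for t = −2.8 on 75 df it is 7.84/(7.84 + 75) = 0.095. The two results cannot be told apart from this figure or its interval.

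**3. Interval against test.** For the equal-tailed interval, the lower limit of λ solves P(F′ ≥ F_obs | λ) = 0.025, or is 0 if there is no solution. The upper limit solves P(F′ ≤ F_obs | λ) = 0.025. Each is converted by η² = λ/(λ + N) with N = 80. At λ = 0 the tail probability is p itself, so the lower limit is 0 whenever p ≥ 0.025. The signed difference is t × 2/√80 = t × 0.2236 in residual SDs, with limits (t ± t_crit) × 0.2236.

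| df | p | F | partial η² | 95% CI | 90% CI | adjusted difference (SD), 95% CI |
|---|---|---|---|---|---|---|
| 70 | 0.03 | 4.907 | 0.066 | 0.000 to 0.181 | 0.003 to 0.158 | 0.495, 0.049 to 0.941 |
| 75 | 0.04 | 4.368 | 0.055 | 0.000 to 0.172 | 0.001 to 0.150 | 0.467, 0.022 to 0.913 |
| 75 | 0.026 | 5.159 | 0.064 | 0.000 to 0.185 | 0.004 to 0.162 | 0.508, 0.062 to 0.953 |
| 75 | 0.024 | 5.308 | 0.066 | 0.0002 to 0.187 | 0.0045 to 0.165 | 0.515, 0.070 to 0.961 |

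The upper limit in the first row is 17.652/(17.652 + 80) = 0.181. The interval leaves zero at p = 0.025. The same switch appears with F(2,70), with N = 52 and F(1,49), and with N = 20 and F(1,15). In each row the signed difference has a 95% interval that excludes zero, in agreement with the unadjusted test.

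**4. How often.** For one unadjusted NET-versus-TAU test at N = 80 with 70 residual df, λ = 80(d/2)². The probability of 0.025 < p < 0.05 is:

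| true d | λ | probability |
|---|---|---|
| 0.3 | 1.80 | 8% |
| 0.5 | 5.00 | 12% |
| 0.635 (80% power) | 8.06 | 9% |
| 0.85 (planning value) | 14.45 | 3% |

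The value 0.85 was set for NET against the waiting list. The Sample size calculation expects TAU to have some effect, so a smaller d against TAU is a fair scenario.

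**5. Effect of Holm.** The last two Holm thresholds are 0.025 and 0.05. A raw p between them can be rejected only at the final step, after every other hypothesis in the family has been rejected.

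**The case against.** Partial η² is a recognised effect size for analysis of covariance, and choosing it changes no test, error rate or sample size. The article does not forbid reporting adjusted means as well, and it does not make partial η² the criterion for clinical significance. That criterion is a separate matter which a change of effect measure would not settle. With one numerator df, a reader can also recover the absolute difference in residual SDs from partial η², N and the df. All of this stands, and it limits the weight of the point. It does not remove it: the article has chosen an effect measure and an interval, and the chosen pair carries neither sign nor scale points.

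Three stronger readings might be inferred, and the documents do not support them.

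- *The interval will contradict the test whenever p lies between 0.025 and 0.05.* This assumes the noncentral-F construction, which the article does not name. A percentile bootstrap in one simulated data set with p = 0.04 gave 0.001 to 0.175, which excludes zero. Such an interval can hardly ever include zero, so it does not mirror the test either. Holm, where applied, confines the conflict to the largest p-value in a family.
- *A result favouring TAU would look the same as one favouring NET.* This is true of partial η² alone. The descriptive means planned under Basic analyses would show direction and a raw difference.
- *The trial cannot show clinical benefit.* The limit belongs to the planned estimate and its interval, not to everything that could be reported.

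**Conclusion.** The point holds as a weakness in the stated effect measure. It is worth correcting but does not affect the validity of the tests. At every p-value, the only treatment-effect estimate with an interval is unsigned and unit-free, while the main hypothesis is directional and clinical. This part needs no distributional assumption.

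The mismatch between interval and test is secondary and conditional. It requires the equal-tailed noncentral-F interval, a raw p between 0.025 and 0.05, and either no multiplicity adjustment or the last Holm step. On those terms, with N = 80 and 40 per arm, its single-test chance is about 8% to 12% for d from 0.3 to 0.635 and 3% at the planning value of 0.85.

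**What to change.** In Effect evaluation, name as the main estimate for each primary and secondary outcome the covariate-adjusted NET-minus-comparator mean difference in scale points with its 95% CI, and give a standardised version (for example, divided by the pooled baseline SD). Keep partial η² only as a supplement. If its interval is meant to match the F test at 0.05, make it a 90% interval and state the construction method.

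The cost is wording only. The same model already yields the adjusted difference and its standard error, and no data collection, test or sample size changes.

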#### Moderator and mediator analyses

Analyses of the potential mediating and moderating factors will be carried out employing methods of conditional process analysis, based on [68, 69]. The end result will be presented as a process model of the effects of NET on PTSD and other symptom measures.

### Ethical issues

The Regional Ethics Committee of Tampere University Hospital has approved the study (R14065, 6/2014), deeming it ethically acceptable and fulfilling the requirements of the Finnish Medical Research Act (488/1999) and the corresponding Decree (986/1999).

Age-specific brochures with information about the study have been prepared for the participating children and their guardians, and translated into several languages. Written consent will be requested from both parents or guardians and the children themselves.

The anonymity of the subjects will be guaranteed by removing identity information when analyzing the data. All data with names and identity information will be destroyed after a period of five years. The data protection ombudsman has been notified of the data collection procedures and the formed register of personal data in line with the Finnish Personal Data Act (523/1999), §10 and §14. The trial has been registered as clinical trial number NCT02425280 in the ClinicalTrials.gov Protocol Registration System on 15 April 2015.

Adherence to the treatment paradigm and procedures will be guaranteed by instructing clinicians to adhere to the NET manual as strictly as possible and by organizing semiannual supervisory meetings.

Interim analyses of differences in treatment outcomes between NET and TAU will be carried out after all measurements are available from the first 20 participants. If, at this time, NET treatment is found to be performing worse than TAU to a clinically significant extent, the trial will be stopped due to ethical concerns.

